## BACKGROUND

1

Over 14.9 million babies are born prematurely across the world every year, and the number is still increasing (Heinonen et al., 2016). Due to immature gastrointestinal function, premature newborns especially those born before 34 weeks, are susceptible to feeding intolerance (FI) (Asadi et al., 2019), and its morbidity could achieve 70% (Ng et al., 2019). Currently, there is no universal definition of FI, the widely accepted one is the following: the gastric residual volume (GRV) was 50% greater than the last feeding volume, with abdominal distension or vomiting (Moore & Wilson, 2011).

FI could badly influence newborns' health. During the neonatal period, it may lead to malnutrition, delayed enteral nutrition, prolonged hospitalization, growth restriction and increase the risk of sepsis and serious gastrointestinal complications such as necrotizing enterocolitis (NEC) (Meister et al., 2019; Neu, 2007). Additionally, it may lead to long‐term negative outcomes such as visceral obesity, glucose intolerance, and increased risk of cardiovascular disease, negative neurodevelopmental outcomes in adulthood (Asadi et al., 2019). At present, treatment for FI includes breastfeeding, modifications in feeding regimes, use of probiotics or medicine, but effectiveness and safety of these methods remain controversial (Basu & Smith, 2020; Fanaro, 2012; Sukwuttichai et al., 2021), feeding intolerance (FI) is still a thorny issue affecting the prognosis of preterm infants. So it is important to find an effective way to cure FI, contributing to recovery of gastrointestinal function and improving long‐term health of preterm infants.

In recent years, massage therapy has been frequently used in neonatal wards for the prevention of FI. Studies have shown that massage could prevent gastric retention and abdominal distention in premature infants, and reduce the length of stay. In addition, massage could stimulate the digestive system and the vagus nerve in premature infants, potentially improving their physical growth (Diego et al., 2007; Heinonen et al., 2016; Tekgündüz et al., 2014). However, there is no consensus on the efficacy of massage in the treatment of FI.

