### Participants: Inclusion/exclusion criteria

3.3

Table 1 specifies the criteria for inclusion, exclusion, termination and exit criteria. Inclusion and exclusion criteria were defined according to previous literature (Baldassarre et al., 2019; Ng et al., 2018; Yakobson et al., 2020).

**TABLE 1 nop21733-tbl-0001:** Inclusion, exclusion, termination and exit criteria.

*Inclusion criteria*
Meet the FI diagnostic criteria
Admitted to the Neonatal Treatment Center of the Affiliated Children's Hospital of Chongqing Medical University within 24 h after birth
28 weeks ≤ gestational age ≤ 34 weeks, 1000 g ≤ birth weight ≤ 2000 g
In clinically stable condition
The neonate's guardians are willing to participate in this trial
*Exclusion criteria*
Apgar score less than 4 at 5 min
Neonates with skin disease, intestinal obstruction, sepsis, necrotizing enterocolitis, gastrointestinal malformation, congenital heart disease, central nervous system disorder, immune deficiency, or any other disease that may affect the ability to eat and normal growth before recruitment
Neonates who need surgery which requires general anaesthesia (except for ligation of patent ductus arteriosus) before the day of randomization
Neonates whose blood pressure is not stable (using dopamine <5 mg /kg/min is permitted)
Ventilator dependent or FiO_2_ (Fraction of inspired oxygen) > 40% on the day of randomization (continuous positive airway pressure, nasal intubation, oxygen mask are allowed)
Neonates who are diagnosed with Grade III or IV ventricular haemorrhage (IVH) on the day or before randomization
*Termination criteria*
Discharge in a stable condition with doctor's advice
*Exit criteria*
Death or discharge before achieving total enteral nutrition
Guardian request to withdraw from the trail

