### Randomization and blinding

3.6

A third‐party personnel created a randomization schedule which was stratified by birth weight (1000–1499 g and 1500–2000 g) using a computer, and then provided it in sealed, opaque, consecutively numbered envelopes. Participants were assigned randomly to one of the two groups by opening the next envelope sequentially from the appropriate set. An independent research assistant responsible for randomization would inform the massager to perform massage when a neonate was assigned to the massage group, and he is the only person aware of which group the neonate had been assigned to. The massager also knows the list of massage groups. Both of them have no access to data of participants and are not responsible for statistical analysis. A researcher who has no access to the allocation group will perform all the assessments for our study.

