### Variables studied

3.7

A researcher who has no access to the allocation group will perform all the assessments for our study. Table 2 shows the demographic variables including maternal characteristics and neonatal characteristics of participants recruited in our trial.

**TABLE 2 nop21733-tbl-0002:** Demographic variables.

Variables	Values
*Maternal characteristics*	
Caesarean delivery	Yes/no
Twin pregnancy	Yes/no
Gestational hypertension	Yes/no
Diabetes during pregnancy	Yes/no
Intrauterine distress	Yes/no
*Neonatal characteristics*	
Gestational age	Weeks
Day of recruitment	Day
Birth weight	g
Boy	Yes/no
Apgar score at 5 min	1–10
Weight at recruitment	g
neonatal critical illness score	Yes/no
Routine treatment received	Antibiotics/caffeine citrate/type of feeding

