#### Primary outcome

3.10.1

The time (day) from initiation of enteral nutrition to total enteral nutrition, which is defined as a daily intake of ≥120 mL/Kg/day (Abdallah et al., 2013).

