### Statistical analysis

3.12

After the data for the entire sample has been collected, it will be performed using SPSS 25.0 software package. Missing data will be forecasted and filled using multiple imputations. A logistic regression model will be used to adjust for multiple potential confounders plain. Measurement data obeying the normal distribution will be expressed as mean (standard deviation), and t‐test will be used for comparing between two groups. Non‐normally distributed variables will be expressed as median (interquartile range), and compared by the use of non‐parametric Wilcoxon–Mann–Whitney test. Classification data will be described as cases count (construct Proportional) and compared using the chi‐square test or non‐parametric Wilcoxon–Mann–Whitney test. The confidence interval will be set at 95%. *p* < 0.05 will be considered statistically significant.

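### No analysis stated for days to full enteral nutrition uses gestational age, so available precision on the primary outcome is given up

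*Protocol article*

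**What the plan says.** The primary outcome (section 3.10.1) is the number of days "from initiation of enteral nutrition to total enteral nutrition".

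Section 3.12 fixes the comparison by the distribution of the variable. If it is normal, a t-test "will be used for comparing between two groups"; if not, a Wilcoxon–Mann–Whitney test replaces it. The same section plans a logistic regression to adjust for several potential confounders, but names neither the confounders nor the outcome to be modelled.

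On gestational age, the article says four things:

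- The Background states: "Due to immature gastrointestinal function, premature newborns especially those born before 34 weeks, are susceptible to feeding intolerance".
- Table 1 admits infants with "28 weeks ≤ gestational age ≤ 34 weeks".
- Table 2 lists "Gestational age" among the neonatal characteristics, in weeks. Table 3 schedules it on CRF1 at baseline and at randomisation.
- Section 3.6 says that a third party "created a randomization schedule which was stratified by birth weight", in two bands (1000–1499 g and 1500–2000 g).

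**The concern.** The article gives a biological reason to expect that maturity matters for feeding, enrols infants across six weeks of gestation, and has each infant's gestational age before treatment starts. The tests it names for an outcome in days cannot use that value. The logistic model cannot use it for this outcome either, unless the day count is dichotomised, and no dichotomy is planned.

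This differs from the choice of model family and from the use of the stratification factor. A linear model containing only the birth-weight stratum would settle both of those and still leave gestational age out.

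What is at stake is precision. Outcome variation that gestational age could explain stays in the error term, which widens the confidence interval and lowers power. With a requirement of 41 infants per arm, that could matter.

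**Working it through.** **Inputs from the article (section 3.4).** Means 28.3 and 33.5 days, so the difference is 33.5 − 28.3 = 5.2 days. 41 per arm before loss; 20% loss; 52 per arm, 104 in total. Stated α 0.025 and power 0.9; printed z values 1.64 and 0.84. No numerical SD is given. Section 3.12 judges significance at p < 0.05.

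**The plan's own figures.** The loss step reproduces: 41/(1 − 0.2) = 51.25, rounded up to 52 per arm. The 41 cannot be reproduced without an SD, so I invert n = 2·[SD·(zα + zβ)/δ]² to find the SD it implies, SD = δ·√(n/2)/(zα + zβ):

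- Stated α read as one-sided 0.025, power 0.9: 5.2 × √20.5/(1.96 + 1.28) = 7.26 days.
- Printed z values: 5.2 × √20.5/(1.64 + 0.84) = 9.49, about 9.5 days.

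These two SDs serve as scenarios. Their disagreement is a separate matter.

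**Assumption.** R² is the share of outcome variance that gestational age explains beyond birth-weight stratum. The article gives no value. I use 4% (a correlation of 0.2) to 30%, taking each SD as the spread left after the stratum.

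**Formulas.** Adjusted SD = SD·√(1 − R²). Equivalent unadjusted sample size = 41/(1 − R²). Power is from the noncentral t distribution with 41 per arm, two-sided 5%, difference 5.2, and noncentrality 5.2/(adjusted SD × √(2/41)).

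| R² | Fall in standard error | 41 per arm act as | Power, SD 7.26 | Power, SD 9.5 |
|---|---|---|---|---|
| 0 | 0% | 41 | 89.3% | 68.7% |
| 4% | 2% | 43 | 90.5% | 70.5% |
| 10% | 5% | 46 | 92.2% | 73.3% |
| 20% | 11% | 51 | 94.8% | 78.2% |
| 30% | 16% | 59 | 96.9% | 83.3% |

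Example, SD 9.5 and R² 30%: adjusted SD = 9.5 × √0.7 = 7.95; noncentrality = 5.2/(7.95 × 0.221) = 2.96; power 83.3%.

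**Gain in power.** SD 7.26: 90.5 − 89.3 = 1.2 points, up to 96.9 − 89.3 = 7.6. SD 9.5: 70.5 − 68.7 = 1.8 points, up to 83.3 − 68.7 = 14.6.

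The normal approximation gives nearly the same gains at R² 4%: 90.0% to 91.1% with SD 7.26, and 69.8% to 71.6% with SD 9.49.

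**The case against.** The strongest reply is that nothing stated here is wrong. After randomisation an unadjusted comparison is valid, section 3.12 does announce adjustment for confounders, and a covariate list is something an article may leave to a fuller document. Much of this stands. Omitting the list would not by itself be a finding. What remains is a choice that the article does state: tests that take no covariate, plus a model type that does not fit an outcome in days. Adding gestational age to the logistic model's list would not bring it into an analysis of days.

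A second reply is that the benefit may be small. This also stands. The Background speaks of susceptibility to feeding intolerance before 34 weeks. It gives no gradient within 28 to 34 weeks and no link to days to full feeding, and every enrolled infant already has feeding intolerance. Birth-weight stratification also balances gestational age in part. The low end of the range above is therefore a real possibility.

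Three stronger readings are tempting, and the article does not support them:

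- **That randomisation is deficient because gestational age is not a stratum.** One stratification factor is a reasonable choice for 104 infants.
- **That imbalance in gestational age is certain to go uncorrected.** The article plans some confounder adjustment and does not exclude gestational age from it. The difficulty is that the model named does not suit the primary outcome.
- **That chance imbalance adds error of its own to the estimate.** Under the same kind of assumptions, its 95% range with 52 per arm is 1.96·√R²·SD·√(2/52): about ±0.9 days (R² 10%, SD 7.26) to ±2.0 days (R² 30%, SD 9.5). This is part of the ordinary sampling error. The unadjusted 95% interval, with half-width about 2.8 or 3.65 days for the two SDs, already contains it, so it should not be set against the 5.2 days as an extra harm.

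**Conclusion.** The point holds as lost efficiency. As the article stands, gestational age is used in no stated analysis that fits the primary outcome, although it is collected and has a stated biological rationale. The unadjusted comparison of the randomised groups remains unbiased with its type I error intact.

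The gain forgone is about 1 to 8 points of power if the SD is about 7.26 days and about 2 to 15 points if it is about 9.5. It is slight at the low end of R² and worth having at the high end. The range rests on an R² of 4% to 30% beyond birth-weight stratum and on SDs inferred from the sample size, none of which the article gives. It is calculated for a linear model against the t-test; a rank test or a time-to-event model would give somewhat different figures. This is a recommended improvement, not an error that invalidates the trial.

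**What to change.** In section 3.12, name one primary model suited to an outcome in days, either linear or time-to-event. Include treatment, birth-weight stratum and gestational age as a continuous covariate, all prespecified. Use gestational age as it is recorded: Table 2 gives the unit as weeks, and the article does not show that days are captured. Keep the t-test or Wilcoxon–Mann–Whitney comparison as a supportive analysis. Restrict the logistic model to binary outcomes, or delete it.

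The cost is a sentence or two. No extra infants or measurements are needed, since gestational age is already on CRF1, and randomisation does not change. The covariates should be fixed in writing before anyone sees outcome data by group, so that they cannot be chosen by their effect on the result. Section 3.14 reports recruitment still open when the article was submitted.

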### Validity and reliability

3.13

An impartial scientific and administrative Steering Committee will monitor the whole course of the study, the evaluation of new information, patient safety, and protocol adherence. Cronbach's alpha is used to calculate reliability. Cronbach's alpha will be calculated for each dimension to assess the consistency of researchers evaluating neonates' condition. Cronbach's alpha between 0.7 and 0.8 is regarded as acceptable and 0.8 or higher is optimal (Cronbach, 1951).

Data monitoring committee (DMC) is responsible for making sure that researcher performs the recruitment, clinicians document data of participants and trial statisticians are blinded to the allocation group until the results are finalized. The DMC also discusses interim analyses and considers protocol modifications during the study period.

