#### Secondary outcome

3.10.2

Days of vomiting, gastric retention (measured by aspirating with a 5‐mL syringe before each feeding) and abdominal distension (defined as a 24‐h abdominal circumference increase of ≥1.5 cm).Weight gain (kg), change of length and head circumference during hospitalization.Length of hospital stay (day).Change of abdomen circumference, gastric retention volume and frequency of defecation (comparison between day 1 and day 7).

Disappearing of vomiting, abdominal distention gastric retention and the amount of milk increased day by day are seemed as alleviation of FI (Lu & Lan, 2020).

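### Cronbach's alpha, chosen to judge consistency between researchers, describes the average of several raters and is blind to rater offsets, while the outcomes are single readings

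*Protocol article*

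**What the plan says.** Section 3.13 (Validity and reliability) names one reliability statistic: Cronbach's "alpha is used to calculate reliability". The section adds that "alpha will be calculated for each dimension to assess the consistency of researchers evaluating" the infants' condition, and its grading is that "alpha between 0.7 and 0.8 is regarded as acceptable and 0.8 or higher is optimal". No other agreement coefficient is named, and the number of raters is not stated.

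The article is not consistent on who takes the readings:

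- Sections 3.6 and 3.7 both state: "A researcher who has no access to the allocation group will perform all the assessments for our study".
- Table 3 in section 3.11 assigns measures to staff roles. Weight, length, head circumference, abdominal circumference and gastric residual volume go to a neonatal nurse. Defecation frequency and the durations of distension and vomiting go to a neonatal physician.

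The secondary outcomes in section 3.10.2 are physical measurements and their changes, a frequency, and numbers of days. Distension is "defined as a 24‐h abdominal circumference increase of ≥1.5 cm".

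**The concern.** Alpha was built for the internal consistency of a multi-item scale, and the article describes no such scale as an outcome. Treating raters as the items is possible, but then two properties matter.

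- Alpha describes the average across all raters in the exercise. The trial describes no averaging; each recorded value is one person's reading. The 0.7 and 0.8 bands are therefore read against a quantity that is more favourable than the one used.
- Alpha depends only on variances and covariances. A rater who always reads higher by a constant leaves it unchanged.

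At stake is a reliability figure that could be labelled optimal while a single reading is only moderately reliable, or while two raters differ systematically.

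**Working it through.** The bands are conventional benchmarks, so there is no derived figure to reproduce. The inputs from section 3.13 are the alpha values 0.70 and 0.80. The number of raters k, the size of any offset and the standard deviations are not in the article. They are assumptions here.

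**1. What the bands mean for one rater.** Alpha with raters as items equals the consistency reliability of the mean of k raters. Inverting Spearman-Brown:

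single-rater consistency = alpha / (k − (k − 1) × alpha)

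| alpha | k = 2 | k = 3 | k = 4 |
|---|---|---|---|
| 0.80 | 0.80/1.20 = 0.67 | 0.80/1.40 = 0.57 | 0.80/1.60 = 0.50 |
| 0.70 | 0.70/1.30 = 0.54 | 0.70/1.60 = 0.44 | 0.70/1.90 = 0.37 |

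The single-rater figure is the lower one for every k of 2 or more and any alpha between 0 and 1.

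**2. A constant offset, in SD units.** Take k = 2 with alpha held at 0.80, so that the infant variance is 2/3 and the error variance 1/3 of a single rating's variance. With an offset of d SD between the raters, the rater variance term is d²/2, and

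absolute-agreement single-rater ICC = (2/3) / (1 + d²/2)

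| d | 0 | 0.5 | 1 | 1.5 | 2 |
|---|---|---|---|---|---|
| alpha | 0.80 | 0.80 | 0.80 | 0.80 | 0.80 |
| ICC | 0.67 | 0.59 | 0.44 | 0.31 | 0.22 |

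A simulation with 200,000 subjects and two raters gave the same values.

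**3. An illustration in centimetres.** Assume two raters 1.5 cm apart (rater variance 1.5²/2 = 1.125) and a random error SD of 0.3 cm (variance 0.09).

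- Between-infant SD 1.5 cm: alpha = 2.25/(2.25 + 0.045) = 0.98; ICC = 2.25/(2.25 + 1.125 + 0.09) = 0.65.
- Between-infant SD 2.5 cm: alpha = 6.25/(6.25 + 0.045) = 0.99; ICC = 6.25/(6.25 + 1.125 + 0.09) = 0.84.

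**4. When an offset reaches an outcome.** Let the true circumferences be C1 and C2, and the offsets of the people reading them b1 and b2. The recorded change is (C2 − C1) + (b2 − b1). If one person takes both readings, b2 = b1 and the offset cancels. If two people do, the difference in offset enters in full. Table 3, which assigns roles, allows the second case; sections 3.6 and 3.7 imply the first.

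**The case against.** The strongest reply is that the consequence is small. The distension criterion is a change within one infant, and most other measured secondary outcomes are changes too, so a constant offset matters only if assessors switch within an infant. If one researcher makes every assessment, they do not switch. That reply stands, and the offset argument must carry the condition. It does not touch step 1, because a single reading is still less reliable than the average that alpha describes.

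It can also be said that the article speaks of consistency, and alpha is a consistency coefficient. That is true, but it is the consistency of an averaged rating, which the trial does not use.

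The reference to dimensions might point to an instrument set out in a fuller protocol; Table 2 lists a neonatal critical illness score whose structure is not described. This cannot be excluded. Even so, alpha across the items of a score would not measure consistency between researchers, which is the stated purpose.

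A reader might infer more than the article supports:

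- **That a missed offset means retraining would be withheld.** Section 3.13 attaches labels to ranges and no action to any value.
- **That assessors in this trial differ by 1.5 cm.** Nothing in the article says so. The 1.5 cm offset is five times the assumed random error and was chosen to equal the distension criterion.
- **That the treatment comparison is biased.** The assessor is described as having no access to the allocation, so offsets should be unrelated to arm.

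**Conclusion.** The point holds as a limited one. Section 3.13 fixes a statistic and bands that do not describe the reliability of the single readings the trial records. A full analysis plan could add detail, but it would not make alpha the right quantity.

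The inversion needs only k: in the best case considered, two raters, the optimal band begins at a single-rater consistency of 0.67, and with four raters at 0.50. The offset figures rest on assumed offsets and standard deviations and show a mechanism, not an expected size. Their relevance to the change-based outcomes depends on whether different staff measure the same infant, which the article leaves contradictory.

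The effect stops at the reported reliability and the measurement quality of secondary outcomes. The primary outcome is days to a defined intake, and its comparison, the sample size and the type I error do not depend on this choice.

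**What to change.** 1. Reconcile sections 3.6 and 3.7, Table 3 and section 3.13 on who takes each measurement and whether more than one person may measure the same infant. If one researcher does everything, no between-researcher coefficient of any kind can be computed from the trial readings alone.
2. On the ratings by more than one researcher that the planned alpha already requires, replace alpha with a two-way, single-measure, absolute-agreement ICC with 95% CI for abdominal circumference, gastric residual volume, length and head circumference. Use kappa for the daily presence of vomiting, distension and retention. Report the number of raters.
3. Apply the reliability bands to those statistics.

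This needs no ratings beyond those a between-researcher alpha would need. The article does not describe how such ratings are obtained, so step 1 must come first. The cost is that the reported reliability will probably be lower.

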### Current study status

3.14

The experiment is still ongoing at the time of submission of this paper; however, subject recruitment began in April 2021. Currently, the study has not completed the recruiting phase, and it is anticipated that the experiment will complete in December 2023.

